### **10.3 Assessment of (Serious) Adverse Events**

The investigator will promptly review documented AEs and abnormal test findings to determine if

- the abnormal test finding should be classified as an AE,
- if there is a reasonable possibility that the AE was caused by the investigational drug or study treatment(s), and
- if the AE meets the criteria for an SAE.

The assessment by the investigator with regard to the study drug relation is done according to the following definitions:

#### No reasonable causal relationship

There is no reasonable causal relationship between the administration of the study drug and the event.

- no temporal relationship to drug administration
- other drugs or chemicals or underlying disease provides definite explanations

#### Reasonable causal relationship

There is a reasonable causal relationship between the administration of the study drug and the event. The time sequence and the evaluation of other elements of the AE show that there is a possible causal relationship with the study drug.

Reasonable causal relationship may be further defined as:

#### Possible

An AE, which

- occurs within a reasonable time sequence to administration of the drug
- but could also be explained by concurrent disease or other drugs or chemicals

#### Probable

An AE, which

- occurs within a reasonable time sequence to administration of the drug
- is unlikely to be attributed to concurrent disease or other drugs or chemicals

#### Definitely

An AE, which

- plausible time relationship to IMP administration
- cannot be explained by concurrent disease or other drugs or chemicals

### **10.4 Reporting of Serious Adverse Events**

The Principal Investigator from each study site is responsible for SAE reporting to the Sponsor according to the following details:

- Reporting to the Sponsor any SAE:
  - **without delay within 24hours** by [contact]), E-Mail ([contact]) or during the weekend (Saturday and Sunday) by Mobile-Phone ([contact])
- Reporting to local IEC of non-fatal and not life-threatening SAEs if evaluated as "suspected", "unexpected" and "drug related" (SUSAR):
  - - **promptly** and no later than **15 calendar days** following awareness that event meets criteria for a SUSAR by FAX or E-Mail as specified by the local IEC. Reporting to local IEC of fatal and life-threatening SAEs if evaluated as "drug related" (SADR) or "suspected", "unexpected" and "drug related" (SUSAR):
    - **without delay** and no later than **7 calendar days** following awareness that event meets criteria for a SUSAR by FAX or E-Mail as specified by the local IEC.
    - follow-up information regarding the SUSAR within **further 8 calendar days**.
- All other SAEs will be summed up in the **annual safety update report**.

The Sponsor is responsible for SUSAR reporting to Swissmedic according to the following details:

- Reporting to Swissmedic of fatal and life-threatening SAEs if evaluated as “suspected”, “unexpected” and “drug related” (SUSAR):
  - **without delay** and no later than **7 calendar days** following awareness that event meets criteria for a SUSAR;
  - follow-up information regarding the SUSAR within **further 8 calendar days**.
- Reporting to Swissmedic of non-fatal and not life-threatening SAEs if evaluated as “suspected”, “unexpected” and “drug related” (SUSARs):
  - **promptly** and no later than **15 calendar days** following awareness that event meets criteria for a SUSAR.
- Sending yearly safety reports, starting one year after the date of notification to Swissmedic. The reports will be drafted by the local Principal Investigator of each study site and sent to the Sponsor. These reports should contain:
  - A concise critical summary of the safety profile of the drug studied as well as the safety issues that have arisen;
- - A listing of all SUSARs that have occurred -The accompanying letter provided with the Annual Safety Report should contain a short summary of the status of the clinical trial in Switzerland (number of centres open/closed, number of patients recruited/recruitment closed, and number of SAR/SUSAR. Reporting immediately all suspected new risks and relevant aspects of known unexpected reactions that require safety-related measure.

An unexpected SAE refers to any AE, the nature or severity of which is not consistent with the current version of Legalon® SIL Investigator’s Brochure (see section 10.6 for details).

### 10.5 Follow up of (Serious) Adverse Events

Subjects terminating the study (either regularly or prematurely) with

- reported ongoing SAE, or
- any ongoing AEs of laboratory values or of vital signs being beyond the alert limit

will return for a follow-up investigation. This visit will take place up to 30 days after terminating the treatment period. Follow-up information on the outcome will be recorded on the respective AE page in the eCRF. All other information has to be documented in the source documents. Source data has to be available upon request.

In case of subjects lost to follow-up, efforts should be made and documented to contact the subject to encourage him/her to continue study participation as scheduled. In case of minor AEs a telephone call to the subject may be acceptable.

All new SAE or pregnancies that the investigators will be notified of within 30 days after discontinuation of study medication have to be reported in appropriate report forms and in the eCRF if required.

Follow-up investigations may also be necessary according to the investigator's medical judgment even if the subject has no AE at the end of the study. However, information related to these investigations does not have to be documented in the eCRF but must be noted in the source documents.

## **10.6 Potential risks/adverse events and treatment**

Due the limited size of the patient population with HCV treated with Legalon® SIL, the estimated incidence of possible adverse reactions provided below is based on the balance between the uncertainty of the actual proportions observed and the low absolute number of patients reporting the reaction, in comparison with the control group in controlled studies and taking into account the supposed relationship with treatment:

- Very common: sensation of heat.
- Common: diarrhoea, bilirubin increased, nausea, vomiting, headache.
- Uncommon: abdominal pain, fever, asthenia, shivering, feeling of body temperature change, abdominal discomfort.
- Rare: somnolence.

It should also be considered that the above incidences are not readily transferable to the general HCV patient population (probably with the exception of sensation of heat, diarrhoea and bilirubin increased), as most of the data on which they are based were derived from studies in special patient subgroups, often in critical conditions, such as patients in liver peri- or post-transplant situations.

Sensation of heat, feeling of body temperature change, shivering and fever usually occur during infusions at the beginning of treatment with Legalon® SIL and recede spontaneously on continuation of therapy. Slow infusions of Legalon® SIL might reduce their occurrence.

Bilirubin increase is a transient effect which spontaneously subsides upon Legalon® SIL discontinuation without treatment. Data collected so far indicate that bilirubin increase following Legalon® SIL administration is not accompanied by cholestatic or hepatotoxic effects.

No contra-indications are known other than hypersensitivity to the active substance or to the excipients. No interactions with other medicine or other forms of interaction are known.

The risk for clinically relevant metabolic drug interactions can be considered low based on in vitro studies and supported by clinical data collected in patients receiving Legalon® SIL and other concomitant medications who did not require any dose adjustments.

There are no adequate data from the use of Legalon® SIL in pregnant women and for this reason Legalon® SIL administration during pregnancy and lactation is not recommended.

There are no reported effects on ability to drive and use machines.  
No case of overdose has been reported.

Legalon® SIL is to be administered by intravenous infusions. Thus patients will be exposed to the general risks related to prolonged and repeated catheter insertion. These risks might be mitigated following the “Guidelines for the Prevention of Intravascular Catheter-Related Infections” (20). The Investigators are recommended to strictly adhere to these guidelines.

## 10.7 Assessment of safety laboratory parameters

The laboratory tests listed in Table below will be performed at the laboratory of each study site and the laboratory of [name] in Lausanne. For time points of laboratory sampling refer to the Flow Chart. Laboratory results of the patients will be available to the investigator of each study site and selected abnormal laboratory alerts will be sent automatically to the sponsor within 24 hours. Clinically relevant laboratory values should be commented on lab report print-outs. A clinically relevant value may be either in- or outside the reference range. Out-of-range data judged as clinically significant (CS) by the Investigator has to be report as an adverse event. Clinically relevant abnormal laboratory test results must be confirmed and should be repeated until normalization or stabilization or until an alternative explanation has been found.

| Category             | Test name                                                                                                                                                                                                                                                                                                               |
|----------------------|-------------------------------------------------------------------------------------------------------------------------------------------------------------------------------------------------------------------------------------------------------------------------------------------------------------------------|
| Haematology          | Hematocrit (Hct)
Hemoglobin (Hb)
Red Blood Cell Count/ Erythrocytes
White Blood Cells / Leukocytes
Platelet Count/ Thrombocytes
Diff. Automatic Neutrophils (relative count)
Eosinophils (relative count)
Basophils (relative count)
Monocytes (relative count)
Lymphocytes (relative count) |
| Coagulation          | Prothrombin time (Quick and INR)                                                                                                                                                                                                                                                                                        |
| Chemistry            | AST(GOT)
ALT(GPT)
Gamma GT
Albumin
Total protein
Alkaline Phosphatase (AP)
Sodium
Potassium
Glucose
Creatinine and creatinine clearance*
Bilirubin Total and fractionated                                                                                                                 |
| Lymphocyte subset    | CD3+ Lymphocyte (absolute and %)
CD4+ Lymphocyte (absolute and %)
CD8+ Lymphocyte (absolute and %)                                                                                                                                                                                                                |
| Serum Pregnancy test | Human Serum chorionic gonadotropin                                                                                                                                                                                                                                                                                      |
| Hormones             | TSH                                                                                                                                                                                                                                                                                                                     |
| HCV                  | HCV genotyping assay PCR/LIPA
Plasma HCV RNA (quantitative) with Roche
COBAS TaqMan v1.0 sensitivity range <15
UI/ml                                                                                                                                                                                           |

|            |                                                                             |
|------------|-----------------------------------------------------------------------------|
| HIV        | Plasma HIV RNA (quantitative) Roche COBAS TaqMan v2.0 sensitivity range <20 |
| Drug level | Concurrent ART drug levels
Silibinin drug level                          |

### 10.8 Pregnancy test

Serum pregnancy tests will be performed at screening (Visit 1) and at the final visit (visit 7) for all female patients of childbearing potential.

### 10.9 Physical examination

Complete and target physical examinations will be carried out as described at the Flow Chart. A complete physical exam consists of an evaluation of organ systems with vital signs (including temperature, pulse rate, and systolic/diastolic blood pressure).

Respiratory rate, temperature, pulse rate, and blood pressure will be measured after patients have been sitting comfortably for at least two minutes.

A targeted physical examination includes an evaluation of vital signs and organ systems only associated with adverse event symptoms as needed, and particularly focused on hepatic related events.

Clinically relevant abnormal findings will be reported as adverse events.

### 10.10 Exchange of safety data between sponsor and Rottapharm

The drug safety data and the information regarding the study treatment will be exchanged between Rottapharm Madaus and the Sponsor in accordance to the pharmacovigilance agreement (we refer to the separate document “pharmacovigilance”). This exchange is aimed to ensure both Parties have the necessary information to monitor and evaluate the study treatment safety profile and to fulfill reporting requirements in the territories under their responsibility. The Parties exchange information utilizing the most current version of Medical Dictionary for Regulatory Activities (MedDRA) as recommended by the Maintenance and Support Service Organization (MSSO). Additionally, each Party code, when possible, all suspect and concomitant drugs with the World Health Organization’s, WHO Drug Dictionary (WHO DRUG).

## **11 DATA QUALITY ASSURANCE**

The Sponsor-Investigator is implementing and maintaining quality assurance and quality control systems with written SOPs and Working Instructions to ensure that trials are conducted and data are generated, documented (record), and reported in compliance with the protocol, GCP, and applicable regulatory requirement(s).

Monitoring will be conducted during the course of the study for quality assurance purposes.

Since almost all study-subjects are included in the SHCS, which is internationally recognized for its high and the well-established and maintained structure ([www.shcs.ch](http://www.shcs.ch)), an ongoing data-cleaning is warranted. We therefore not plan to perform primary an audit during the study.

### **11.1 Routine Monitoring**

Regular monitoring visits at the investigator's site prior to the start and during the course of the study will help to follow up the progress of the clinical study, to assure utmost accuracy of the data and to detect possible errors at an early time point.

To achieve this goal, the monitor will carry out the following visits:

- Trial Initiation Monitoring Visit aimed at ensuring the Principal Investigator (PI) and the Staff are properly instructed on how to follow the study protocol and to conduct the trial; this assumes all required essential documents for the trial have been obtained and the IMPs are available at Site
- Monitoring Visits aimed at verifying that the rights and well-being of human subjects are protected; the reported trial data are accurate, complete, and verifiable from source documents; the conduct of the trial is in compliance with the currently approved protocol/amendments, with ICH-GCP, and with all the applicable regulatory requirements.
- Close-out Monitoring Visit aimed at ensuring essential documents are available; arrangements for retention of study and source data have been made; all remaining unused supplies are returned and/or destroyed.

The Sponsor-Investigator organises professional independent monitoring for the study.

All original data including all patient files, progress notes and copies of laboratory and medical test results must be available for monitoring. The monitor will review all or a part of the eCRFs and written informed consents. The accuracy of the data will be verified by reviewing the above referenced documents. The investigator's site will collaborate with the Clinical Trials Center (CTC) of the University Hospital Zurich to ensure regular monitoring. According to the CTC's Monitoring SOP the extent and nature of monitoring activities based on the objective and design of the study will be defined in a study specific Monitoring Plan.

### **11.2 Audits and Inspections**

A quality assurance audit/inspection of this study may be conducted by the regulatory authority or IEC, respectively. The quality assurance auditor/inspector will have access

to all medical records, the investigator's study related files and correspondence, and the informed consent documentation that is relevant to this clinical study.

The investigator will allow the persons being responsible for the audit or the inspection to have access to the source data/documents and to answer any questions arising. All involved parties will keep the patient data strictly confidential.

### **11.3 Specification of Source Documents**

In addition to the medical chart of the patients and the laboratory reports, the following documents are considered source data, including but not limited to:

- SAE worksheets
- Nurse records, records of clinical coordinators, and
- Medical records from other department(s), or other hospital(s), or discharge letters and correspondence with other departments/hospitals, if subject visited any during the study period and the post study period.

Source data must be available at the site to document the existence of the study subjects and substantiate the integrity of study data collected. Source data must include the original documents relating to the study, as well as the medical treatment and medical history of the subject.

The following information (at least but not limited to) should be included in the source documents:

- Demographic data (age, sex)
- Inclusion and Exclusion Criteria details
- Participation in study and signed and dated Informed Consent Forms
- Visit dates
- Medical history, prior concomitant medication and physical examination details
- Key efficacy and safety data (as specified in the protocol)
- AEs and concomitant medication
- Results of relevant examinations
- Laboratory printouts
- Dispensing and return of study drug details
- Reason for premature discontinuation
- Patient ID number

## **12 STATISTICS**

### **12.1 Statistical and Analytical Plans**

The analyses of the primary and secondary endpoints of this non-comparative study will be purely descriptive. The average decline of HCV RNA during the lead-in phase (day +1 to day +15) will be expressed in  $\log_{10}$  IU/ml using methods for left-censored data (Tobit regression) (18) in case of undetectable values are encountered and represents the primary efficacy analysis and will be performed in the evaluable patients. We will further report the percentages (with 95% CI) of patients achieving undetectable levels of HCV RNA at the various time points. We will also attempt to analyse factors associated with  $\log_{10}$  HCV RNA response with mixed effects models (19) taking into account all measured HCV values from day -14 to day + 15. In these models, slopes will be allowed to change at day+1 and day +15. Potential co-factors will be first assessed in univariable and bivariable models to detect interactions and collinearities. Relevant effect modifiers and confounders will then be included in multivariable models. The following co-factors will be considered: age, gender, IL28B genotype, BMI, CD4 values and HIV RNA. We will look at the potential co-factors in univariable models first and only include relevant confounding variables in the multivariable analysis. Safety analyses will be performed including all patients that received at least one dose of the study medication (Safety Population). Adverse events will be reported in percentages (with 95% CI) of patients experiencing an event (for clinical events and abnormal laboratory values considered clinically significant by the Investigator – this represent the primary safety analyses) or the percentages below/above 1x and 2x normal range limits for laboratory values.

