score  $\geq 3$ ), an unfavourable interleukin 28 B genotype and a high baseline HCV viral load. The study results confirmed the efficacy of iSIL in a difficult-to treat patient group and underscored that iSIL could be a valuable treatment-option in patients not responding to PR (12). The potential role of iSIL as rescue therapy in patients not responding to previous combined therapy with PR and a HCV-specific PI was demonstrated by Biermer et al., 9 of the 13 responder patients are in the follow-up period: 3 of them achieved SVR24, 2 achieved SVR12, and 4 had a viral relapse (13). Recent reports also show the efficacy of iSIL in patients with HCV-reinfection after liver transplantation. After 14 days treatment of iSIL in a dosage of 20mg/kg all four patients showed normalization of liver enzymes and a significant decline of HCV-RNA with a mean log-reduction of 2.8 (14). Moreno et al. presented their data about the safety and the anti-HCV activity of a rescue therapy with iSIL in cirrhotic HIV-HCV co-infected individuals at the 19th conference on retroviruses and opportunistic infections (CROI) in 2012. They treated 4 individuals with previous partial response (PR) or relapses to PR with iSIL 20mg/kg for at least 14 days. Three patients started iSIL during PR and nitazoxanide (add-on strategy). Overall, therapy with iSIL led to negative HCV-RNA in 3 subjects and values  $<50$  IU/mL in the remaining. The period of mono-therapy with iSIL produced a time-dependent effect: the mean decrease of HCV-RNA was  $-2.5 \log_{10}$  IU/ml after 1 week and  $-4.62 \log_{10}$  IU/ml after 35 days. However, HCV-RNA rebounded in 4 patients after stopping iSIL. There were no significant adverse events related to iSIL and all patients maintained current antiretroviral therapy (ART) with undetectable HIV RNA (15).

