#### ***Primary endpoints:***

- Frequency of adverse events during iSIL treatment.
- Kinetics of the decline in HCV-RNA after 2 weeks of iSIL treatment (difference in IU/ml from day 1 to day 15, see flow-chart below).

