#### **7.4 Early Withdrawal of Subjects**

The subject has to be withdrawn from the study prior the expected completion if there is a failure of the subject to adhere to protocol requirements.

Any subjects experiencing a serious adverse event felt to be related to study drug should be withdrawn from the study. Subjects will be withdrawn if they require hospitalization for addiction treatment. Any subject withdrawing their consent to participate in the study will be withdrawn from the study. Subjects discontinued from the clinical trial will be scheduled for a final evaluation and given appropriate treatment referrals. Subjects withdrawn may be replaced, at the discretion of the principal investigator.

Subjects will be informed at the consent session that treatment may be discontinued due to:

- The subject withdraws his/her informed consent to participate in the study
- Intolerable side effects
- Significantly abnormal laboratory values confirmed with a repeat testing
- Clinical deterioration for any reason or any clinical status that necessitates hospital admission
- Lost to follow up
- Protocol Violation

Reasons why subjects are discontinued from the clinical trial will be documented on the Study Termination Form, along with any referrals that are made. A final safety evaluation will be conducted as soon as possible on all treated subjects who are discontinued. This will include study-required laboratory testing, physical examination, and urine pregnancy test (women only).

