### **12.3 Handling of Missing Data**

We plan to recruit additional patients in case of drop-outs or extensive missing data to ascertain that there are 20 evaluable patients. We will further evaluate the effect of missing data on study findings by three sensitivity analyses (missing=failure, missing=success, last observation carried forward).

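### The primary efficacy estimate rests on an undefined evaluable subset with replacement, so the size of the HCV RNA decline is at risk of bias, and two of the three missing-data checks cannot test it

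*Protocol*

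**What the plan says.** Section 12.1 defines the primary efficacy analysis on a continuous scale: "The average decline of HCV RNA during the lead-in phase (day +1 to day +15) will be expressed in" log10 IU/ml, with Tobit regression if values are undetectable. It adds that this analysis "represents the primary efficacy analysis and will be performed in the evaluable patients". No section defines *evaluable*. The same paragraph does define a Safety Population, everyone dosed at least once, but uses it only for safety.

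Section 12.3 says: "We plan to recruit additional patients in case of drop-outs or extensive missing data to ascertain that there are 20 evaluable patients". It does not say how much missing data counts as extensive. Section 7.4 puts it differently: "Subjects withdrawn may be replaced, at the discretion of the principal investigator". Section 12.4 speaks of 20 enrolled subjects, not 20 evaluable ones.

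For missing data, section 12.3 names "three sensitivity analyses (missing=failure, missing=success, last observation carried forward". Section 12.1 also has a binary summary: "We will further report the percentages (with 95% CI) of patients achieving undetectable levels of HCV RNA at the various time points". A mixed model using all HCV RNA values appears in section 12.1, but only to explore factors associated with response.

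Section 5.1 words the endpoint as a "difference in IU/ml from day 1 to day 15", without the logarithm. This point uses the log10 scale of section 12.1.

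**The concern.** Under section 7.4, non-adherent subjects have to be withdrawn and those with a drug-related serious adverse event should be. Treatment may also be stopped for intolerable side effects, confirmed abnormal laboratory values or clinical deterioration. Such patients receive less drug, and section 4.5 describes a decline that continues through the two weeks, so a smaller day-15 decline in them is the natural expectation. They stay in the safety analysis but can leave the primary efficacy analysis and be replaced.

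The trial is open-label (section 8.7), HCV RNA is measured at every visit (Study Schedule), and laboratory results are available to site investigators (section 10.7). Without a definition, evaluability and replacement can be decided with the outcome in view.

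What is at stake is the size of the decline. Section 4.5 argues from a mean fall of about 3 log10 to better chances of sustained response and less telaprevir resistance, and section 5.1 sets the aim for the lead-in course as such, not for the patients who stay evaluable.

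**Working it through.** **The plan's own figure.** The number 20 has no derivation to reproduce: the protocol gives no target effect, standard deviation, power or drop-out rate, and section 12.2 marks hypotheses as not applicable.

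**Inputs.**
- Decline in the 20 evaluable patients: 3.02 log10, from the 20 mg/kg group of the earlier study cited in section 4.1.
- Standard deviation: 1.01, from the same place, reading the ± figure as a standard deviation.
- Number of replaced drop-outs, k, and their mean day-15 decline, m: not in the documents, so varied.

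**Precision at n = 20.** Half-width = t(0.975; 19) × SD/√n = 2.093 × 1.01/√20 = 0.47 log10, an interval of 2.55 to 3.49. Power against zero decline is about 100%.

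**Effect of leaving drop-outs out.** All-treated mean = (20 × 3.02 + k × m)/(20 + k). Overstatement = 3.02 minus that mean.

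| k | m | All-treated mean | Overstatement |
|---|---|---|---|
| 0 | – | 3.02 | 0 |
| 2 | 1.5 | (60.4 + 3)/22 = 2.88 | 0.14 |
| 4 | 0 | 60.4/24 = 2.52 | 0.50 |
| 4 | 3.02 | 3.02 | 0 |
| 4 | 4.0 | (60.4 + 16)/24 = 3.18 | −0.16 |
| 5 | 0 | 60.4/25 = 2.42 | 0.60 |
| 5 | 4.0 | (60.4 + 20)/25 = 3.22 | −0.20 |

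For up to five drop-outs and m between 0 and 4, the error runs from +0.60 to −0.20 log10.

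**The three sensitivity rules.**
- *Missing=failure and missing=success* need a binary outcome. The protocol sets no success threshold for the log10 decline, so these rules supply no number for it. They do work for the undetectable percentage. If 15 of 20 evaluable patients were undetectable and four others had dropped out, 75% becomes 15/24 = 62.5% or 19/24 = 79.2%.
- *LOCF* can be computed on log10 values. Under an assumed linear fall of 3.02 over 14 days, the carried value is 3.02 × (day − 1)/14: 0.65 at day 4, 1.51 at day 8, 2.37 at day 12. Each is below 3.02, so LOCF understates what continued drug would be expected to give. It errs the other way if RNA has risen again by day 15. Section 4.4, on four co-infected patients, reports that "HCV-RNA rebounded in 4 patients after stopping iSIL".

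**The case against.** The study is single-arm and descriptive, with no hypothesis to test and a stated focus on safety. The co-primary safety analysis already includes everyone dosed. Infusions are supervised daily for only 14 days, so drop-outs may be few. With power against zero near 100%, no stated conclusion turns on the analysis set. An analysis plan that is not shown may define *evaluable*. All of this stands and limits the severity. It does not remove the point, because the protocol itself commits the primary estimate to a subset and to recruiting until that subset is full.

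The checks are also not empty. LOCF applies to the endpoint, the binary rules apply to the undetectable percentage, and the exploratory mixed models use all measured values. Section 7.4 gives discontinued treated patients a final evaluation with laboratory testing, and the table in section 10.7 lists HCV RNA among the tests. This stands too. Still, for the mean log10 decline LOCF is the only one of the three named rules that can be used.

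A reader might infer more, in three ways that the documents do not support:
- That the decline *is* biased in favour of iSIL. The protocol gives no drop-out count and no drop-out response, and poor virological response is not a listed withdrawal reason. The sign can reverse.
- That *evaluable* means having completed all 14 infusions. No section says so.
- That LOCF must flatter the drug. Section 4.4 reports rebound without its speed, in patients treated for at least 14 days, three of whom started iSIL on top of other therapy. Full return to baseline within days of an early stop would be an assumption.

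**Conclusion.** The point holds as a risk to the size of one primary estimate. An undefined evaluable set, open-ended replacement and tolerability-related reasons for leaving make an overstated decline the most plausible direction of error. The worst row with four drop-outs (0.50 log10) is about as large as the sampling half-width (0.47). Milder assumptions give 0.14 or less, and no drop-outs gives nothing. These figures rest on the 3.02 and 1.01 of an earlier study and on assumed values of k and m.

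The existence of a decline is not threatened, so this should be fixed but does not invalidate the study.

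**What to change.** In section 12.1:
- Make the primary efficacy set all patients with at least one iSIL dose and a day-1 HCV RNA.
- Estimate the day-15 change from all daily log10 values with a left-censored mixed model.
- Report the evaluable set as supportive, with its definition fixed before the data are reviewed.

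In sections 12.3 and 7.4:
- Align the replacement wording, and state that replacements add to the set and remove nobody.
- Restrict missing=failure and missing=success to binary endpoints.
- For the log10 endpoint, keep LOCF and add beside it a conservative bound in which a missing day-15 value is set to the day-1 value. This bound is deliberately harsh, since it ignores falls already measured. It also covers the mixed model's reliance on values being missing at random.
- Include any HCV RNA measured at the final evaluation of discontinued patients, at its actual sampling date.

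The cost is wording in three sections and slightly more analysis, using samples that the schedule already collects. The estimate may come out less favourable.
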